## Abstract

Technological innovation has revolutionized healthcare, particularly in neurological rehabilitation, where it has been used to address chronic conditions. Smart home and building automation (SH&BA) technologies offer promising solutions for managing chronic disabilities associated with such conditions. This single group, pre-post longitudinal pilot study, part of the H2020 HosmartAI project, aims to explore the integration of smart home technologies into neurorehabilitation. Eighty subjects will be enrolled from IRCCS San Camillo Hospital (Venice, Italy) and will receive rehabilitation treatment through virtual reality (VR) and robotics devices for 15 h per day, 5 days a week for 3 weeks in the HosmartAI Room (HR), equipped with SH&BA devices measuring the environment. The study seeks to optimize patient outcomes and refine rehabilitation practices. Findings will be disseminated through peer-reviewed publications and scientific meetings, contributing to advancements in neurological rehabilitation and guiding future research.

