## 2. Materials and Methods

### 2.1. Study Setting and Design

To ensure the completeness and quality of reporting, we referred to the SPIRIT (Standard Protocol Items: Recommendations for Interventional Trials) [9] guidelines as well as Thabane and Lancaster’s [10] guidance on how to report protocols of pilot and feasibility trials. The protocol was registered in the ClinicalTrials.gov PRS database (Registration number: NCT06270420, https://clinicaltrials.gov/study/NCT06270420, accessed on 22 February 2024). This single group, pre-post longitudinal pilot study will be conducted within the HosmartAI research project (EU Horizon 2020, research and innovation program—grant agreement No 101016834). The trial will last twenty months and will be carried out at the San Camillo IRCCS Hospital (Venice, Italy), within which a smart rehabilitative room (HR) will be created. This room will feature rehabilitation devices complemented by smart-home sensors and actuators developed by VIMAR SpA (Marostica, Italy), all of which send data to a cloud system (Kloud) created by Khymeia Group (Padua, Italy). The purpose of this setup is to develop an innovative solution to monitor various activities that patients can perform autonomously or under therapists’ supervision. This solution aims to assist clinicians in monitoring patients within the hospital, identifying potential risks, and ensuring adherence to therapy protocols. Throughout the pilot phase, stakeholders involved will be closely observed using a persona-based approach, providing valuable insights into the behaviors of therapists and patients, thus enabling the analysis and exploration of the extension of active patient monitoring to the home environment.

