### 2.2. Participants and Eligibility Criteria

The study will enroll 80 subjects among the patients hospitalized at the IRCCS San Camillo Hospital in Venice. Inclusion criteria for enrolment include an age greater than 18 years and a diagnosis of neurological pathology, such as ischemic and/or hemorrhagic stroke, Parkinson’s disease, multiple sclerosis, head trauma, brain tumor, ataxia, post-COVID syndrome, or peripheral neuropathy. Exclusion criteria include non-stabilized fractures, severe depression, significant visual and/or hearing impairments, dementia, uncontrolled epilepsy, severe neglect, and profound comprehension deficits that would hinder interactions with robotic and virtual reality devices.

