### 2.3. Intervention

Subjects were enrolled among hospitalized patients based on the pre-defined inclusion criteria. The identification of eligible subjects was conducted through notification by the Clinical Research Unit at San Camillo Hospital. Subsequently, researchers from the HosmartAI project will enroll and evaluate (T0) the patients, after which they will commence their experimental treatment in the HR room, in addition to their regular daily conventional rehabilitation session. The experimental treatment will be tailored to the subjects’ therapeutic needs and will run for three weeks, comprising 15 one-hour sessions each, conducted five days a week. The specialized devices targeting balance, manual dexterity, and limb functionality, as described in the study setting section, will be utilized during these sessions. Pre-treatment (T0) and post-treatment (T1) assessments will be conducted using validated clinical scales and tests to determine therapy effects. Additionally, device-specific evaluation systems will be employed to assess treatment outcomes. A qualitative analysis will ascertain technology usability, acceptability, and user satisfaction. All assessments and treatments will be administered by qualified physiotherapists. Figure 1 illustrates the participants’ timeline.

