### 2.4. Outcome and Timelines

The primary aim of the study is to verify the productivity of the rehabilitation service at the IRCCS San Camillo Hospital following the sensorization of the HR with the smart-home system’s devices. Productivity outcomes will be measured through treatment performance, physiotherapists involvement, and adverse events. Assessments will be conducted monthly over a period of one year; the specifics are listed below.

Treatment Performance:Direct measurements of treatments provided in the HR, such as number of treatments provided per month; number of times accessed per month by system users (i.e., patients); number of therapy minutes provided per month and overall therapy duration.

Physiotherapist Involvement:The number of physiotherapists providing treatment relative to the number of patients will be quantified. This ratio (number of physiotherapists/number of patients), will reflect the allocation of staff resources during the study period.

Adverse Events:Measurement and recording of adverse events will involve number of falls occurring during the observation period within the HR.

The following secondary outcomes, changes in clinical parameters following therapies conducted in the HR, as well as satisfaction and user experience associated with the therapy, will also be assessed at baseline (T0) and at the end of the treatment, after 3 weeks (T1).

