### 2.5. Sample Size

The study aims to recruit subjects from IRCCS San Camillo Hospital’s Neurorehabilitation Department. With an average occupancy of 60 beds per week, it is estimated that four eligible subjects are admitted monthly. Given a 20-month trial period, the target sample size was set at 80 subjects. To evaluate the reliability of our study’s results, a retrospective (post-hoc) power analysis was conducted using G*Power 3.1.9.6 software (Heinrich-Heine-University Düsseldorf, Germany). With a two-tailed test, a moderate effect size (Cohen’s d) of 0.5, an alpha level of 0.05, and a total sample size of 80, the analysis yielded a calculated statistical power of 0.99. This suggests a strong probability of detecting the expected effects and highlights the potential dependability of our findings.

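### The adverse-event component of the primary outcome counts only falls inside the HosmartAI Room, so a low or zero count would be weak evidence about harm

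*Protocol article*

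**What the plan says.** Section 2.4 of the protocol article states the primary aim as the productivity of the rehabilitation service once the HosmartAI Room (HR) has been fitted with sensors. It measures this through treatment performance, physiotherapist involvement and adverse events. The third component is defined in one sentence: "Measurement and recording of adverse events will involve number of falls occurring during the observation period within the HR". No other type of event and no other place is named.

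The context comes from other sections:

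- Section 2.2, on the setting: "The study will enroll 80 subjects among the patients hospitalized at the IRCCS San Camillo Hospital in Venice".
- Section 2.3, on the dose: the treatment "will run for three weeks, comprising 15 one-hour sessions each, conducted five days a week", and it is given "in addition to their regular daily conventional rehabilitation session".
- The Abstract, on the same dose: "for 15 h per day, 5 days a week for 3 weeks in the HosmartAI Room (HR".
- Section 2.5, on size: "Given a 20-month trial period, the target sample size was set at 80 subjects", from an estimated four eligible admissions per month.
- Section 2.4, on the timing of the productivity outcomes: "Assessments will be conducted monthly over a period of one year".
- Section 2.1, on the purpose of the system, which is partly to "assist clinicians in monitoring patients within the hospital, identifying potential risks".

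The article gives no expected number or rate of falls, no acceptable limit and no comparator for them. Section 3 acknowledges that there is no control group.

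**The concern.** The label of the component is wider than its content. A reader of the results will see a primary-outcome line called adverse events, but the rule behind it admits one event type in one room. A dizzy spell on a virtual-reality device, pain after a robot session or a device fault falls outside it. So does a fall on the ward later the same day, even though the added therapy load could plausibly show itself there.

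This matters because the other two components reward more treatment and a leaner ratio of physiotherapists to patients. Adverse events are the only primary component that could register a cost to patients. Section 3 also says that the findings may guide larger trials and implementation. If the count is low or zero, what matters is how much harm that result could rule out. Exposure in the room is short, so the answer is not much.

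**Working it through.** **The plan's own figure.** The only calculated figure is the power of 0.99 in Section 2.5 (N = 80, d = 0.5, two-sided alpha 0.05). A paired t-test with noncentrality 0.5 × √80 and 79 degrees of freedom gives 0.993, so it reproduces. It does not concern falls, and there is no fall figure to reproduce.

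**Exposure, Section 2.3 schedule.**
- Per patient: 15 sessions × 1 h = 15 h.
- Three-week inpatient time: 21 × 24 = 504 h, assuming the patient stays throughout. Share in the HR: 15/504 = 2.98%.
- All patients: 80 × 15 = 1,200 h = 50 patient-days, against 80 × 21 = 1,680 patient-days of whole courses.
- If only one year is counted: 4 × 12 = 48 patients, 48 × 15 = 720 h = 30 patient-days.

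**What zero falls would rule out.** This step needs no assumed fall rate. The one-sided 95% upper bound is −ln(0.05)/exposure for a Poisson rate and 1 − 0.05^(1/n) for the proportion of patients who fall.

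| | 80 patients | 48 patients |
|---|---|---|
| HR hours | 1,200 | 720 |
| Upper bound per 1,000 HR hours | 2.5 | 4.2 |
| Same, per 1,000 patient-days in the HR | about 60 | about 100 |
| Upper bound, share of patients | 3.7% | 6.1% |

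A two-sided exact interval is a little wider. For 80 patients its upper limit is 3.689/1,200 = 3.1 per 1,000 HR hours, or 4.5% of patients.

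**How likely zero is.** This step does need an in-room fall rate, which the documents do not give. P(0) = exp(−rate × exposure). The rates below are assumptions.

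| Assumed falls per 1,000 patient-days | Expected in 50 patient-days | P(0), 80 patients | P(0), 48 patients |
|---|---|---|---|
| 3 | 0.15 | 0.86 | 0.91 |
| 5 | 0.25 | 0.78 | 0.86 |
| 10 | 0.5 | 0.61 | 0.74 |
| 20 | 1.0 | 0.37 | 0.55 |
| 50 | 2.5 | 0.08 | 0.22 |

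Zero stops being the likelier result above ln(2)/50 days = 13.9 per 1,000 patient-days with 80 patients, and above 23.1 with 48.

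**Falls outside the definition.** At the same assumed 3 to 10 per 1,000 patient-days, the 1,680 patient-days of whole courses would contain 5.0 to 16.8 falls.

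**Sensitivity to the Abstract.** Its wording implies 15 × 5 × 3 = 225 h per patient, or 225/504 = 44.6% of the course and 18,000 h in total. The hourly bound would then be 0.17 per 1,000 HR hours, and P(0) at 3 to 10 per 1,000 patient-days would be 0.105 to 0.001. The per-patient bound stays at 3.7%, because it depends only on the number of patients.

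**The case against.** The case for the plan has real force on several points.

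- **A zero is not assured.** A reader might infer from the 3% share of time that the count is bound to be zero. The documents do not support that. Even at 3 to 10 falls per 1,000 patient-days the chance of zero is 61–86%, not near certainty, and that range is itself an assumption. HR hours are active and include balance work, but physiotherapists administer them, so the hazard per hour could be above or below the ward average. This stands.
- **The article does not claim to demonstrate safety.** A reader might infer that the fall count is meant as proof of safety. Section 2.4 presents it as a productivity measure, and no section says that it will be used to declare the room safe. This stands. The point concerns how a low count may be read.
- **The room is a coherent place to count.** Treatment performance is also measured there, and the sensors are described as detecting falls. Section 2.1 describes what the system should help clinicians do and does not contradict Section 2.4. This justifies keeping HR falls as a named item. It does not justify calling them adverse events without qualification.
- **Other harms may be recorded under the full protocol.** A reader might infer that the trial records nothing else. That cannot be concluded from a condensed article. But the sentence at issue is a stated definition of a primary-outcome component, and reporting elsewhere would not change what that component counts.
- **Ward falls cannot be attributed.** Without a control group, falls across the stay would be mostly background. This stands and limits the fix.

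**Conclusion.** The point holds as a definition that is too narrow for its label. The adverse-event component admits only falls in the HR, so it misses non-fall events in sessions and any fall elsewhere during the course. A low or zero count would be weak evidence: with zero falls, the one-sided 95% upper bound is about 2.5 per 1,000 HR hours or 3.7% of 80 patients, and about 4.2 per 1,000 HR hours or 6.1% if about 48 patients are counted.

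The hourly bounds rest on the Section 2.3 schedule, full attendance and a constant Poisson rate. The per-patient bounds rest only on the number of patients and their independence. The 2.98% share also assumes a full 21-day stay. The 48-patient case assumes that the one-year window in Section 2.4 limits who is counted, which the article does not settle against its 20-month trial period. Any statement about how likely zero is depends on an assumed fall rate.

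**What to change.** 1. Define the component as all adverse events recorded during HR sessions, classified by seriousness and relation to the devices, with falls in the HR as a named subset.
2. Report events per 1,000 sessions or per 1,000 HR hours with exact 95% confidence intervals, so that a zero is shown with its upper limit.
3. Report all inpatient falls between the first and last HR session descriptively, from hospital records (assumed to be available), and state that without a control group they cannot be attributed to HR therapy.
4. Reconcile the session duration in the Abstract with Section 2.3, and the one-year window in Section 2.4 with the 20-month trial period, because both set the denominator.

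The cost is modest. Physiotherapists already administer every session and can log events as they occur; the rest is some data extraction and an amended outcome definition. Treatment does not change.

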### 2.5. Sample Size

The study aims to recruit subjects from IRCCS San Camillo Hospital’s Neurorehabilitation Department. With an average occupancy of 60 beds per week, it is estimated that four eligible subjects are admitted monthly. Given a 20-month trial period, the target sample size was set at 80 subjects. To evaluate the reliability of our study’s results, a retrospective (post-hoc) power analysis was conducted using G*Power 3.1.9.6 software (Heinrich-Heine-University Düsseldorf, Germany). With a two-tailed test, a moderate effect size (Cohen’s d) of 0.5, an alpha level of 0.05, and a total sample size of 80, the analysis yielded a calculated statistical power of 0.99. This suggests a strong probability of detecting the expected effects and highlights the potential dependability of our findings.

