### 2.6. Data Collection and Analysis Plan

Patient data, including clinical and demographic information, will be collected and inputted into treatment devices. A unified cloud platform will consolidate information from SH&BA devices and patient clinical data stored across devices. Data from HR sensors will gauge patient therapy adherence.

Descriptive analysis will be initially conducted on the enrolled subjects’ sample. For each demographic and clinical variable, we will consider the mean, standard deviation [23], absolute frequencies (n), and percentages (%). For each mode of clinical treatment delivery (i.e., depending on the physiotherapist/patient ratio), pre-treatment (T0) and post-treatment (T1) motor performance values will be compared using either Student’s t-test for paired data or the Wilcoxon test, depending on the data distribution, which will be assessed with the Kolmogorov–Smirnov test. To assess the presence of a statistically significant difference in motor recovery in relation to the type of treatment model, the motor outcomes of the patients will be compared by means of parametric or non-parametric independent sample comparison tests (i.e., Student’s t-test for independent data or the Mann–Whitney test), depending on the data distribution. To identify the patient profile that best fits each therapy model, regression models will be utilized, with the type of therapy model as the dependent variable, and assessment scales and anamnestic variables as predictor variables. To define the satisfaction, usability and technology acceptance and clinical profile of patients accessing technological therapy, tests for customer satisfaction will be utilized. The statistical significance is set at *p* < 0.05. Data analysis will be conducted using the free statistical software R Studio, version 4.0.3 [24].

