Future implications include profiling patient suitability for this organizational model and its transferability to other rehabilitation settings. However, it is important to acknowledge the limitations of this study, such as the need for expert physiotherapists and potential enrolment complexities, as well as the inherent constraints of pilot studies, including small sample size, a lack of control groups, and limited generalizability. Nevertheless, despite these limitations, the study’s findings are expected to inform and facilitate similar technology implementations in various rehabilitation medical centers. One of the most significant implications is the potential for personalized therapeutic approaches which could concurrently enhance operational efficiency. Specifically, the implementation of SH&BA therapies within technological group treatments for neurological subjects holds promise for augmenting therapy quantity, thereby potentially improving clinical outcomes [28]. This envisaged scenario would unfold alongside resource optimization efforts, aiming to enhance the precision and reliability of collected data and administered therapies, while also striving to mitigate errors. Furthermore, enhancing the patient experience is indeed a significant aspect. The integration of smart-home technologies provides the potential to enhance the overall patient experience during the rehabilitation process. By offering a more comfortable and familiar environment for therapy, it enables greater autonomy and control throughout the healing journey. Moreover, the consideration of patients’ social interaction during group therapy sessions, which also contributes to clinical improvement, further underscores the holistic approach to patient care [29]. Lastly, the remote monitoring capabilities of these systems could expand access to rehabilitation services, particularly for patients in remote or disadvantaged areas.

Disseminating these results nationally and internationally underscores the project’s significance. Efforts to address these limitations and refine the methodology will be crucial in maximizing the impact and applicability of the study’s findings.

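### The stated power of 0.99 fits one pooled paired test on all 80 patients, which the analysis plan does not contain; the planned between-model comparison has at most 0.60

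*Protocol article*

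**What the plan says.** Section 2.5 sets the sample size from admissions, at four eligible patients a month: "Given a 20-month trial period, the target sample size was set at 80 subjects". It then reports a power calculation. The inputs are "With a two-tailed test, a moderate effect size (Cohen’s d) of 0.5" and "an alpha level of 0.05", and the result is given as "a total sample size of 80, the analysis yielded a calculated statistical power of 0.99". The section names no test, outcome or scale. From the 0.99 it concludes that the expected effects are very likely to be detected and that the findings can be depended on.

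Section 2.6 describes two kinds of hypothesis test on motor outcomes:

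- The T0–T1 comparison is made separately by mode: "For each mode of clinical treatment delivery (i.e., depending on the physiotherapist/patient ratio"). It uses a paired t-test or a Wilcoxon test.
- Motor recovery is compared between treatment models by "parametric or non-parametric independent sample comparison tests", that is, a two-sample t-test or a Mann–Whitney test.

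It describes no T0–T1 test pooled over all patients, and gives neither the number of modes nor how the 80 patients divide among them.

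Section 2.4 makes service productivity the primary aim: monthly treatments, accesses, therapy minutes, the staff-to-patient ratio and falls. Motor scales are secondary. The Discussion lists the constraints of a pilot as "including small sample size, a lack of control groups, and limited generalizability".

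**The concern.** A power figure describes a particular test of a particular outcome. Section 2.5 attaches 0.99 to the study as a whole, and neither kind of motor test in section 2.6 uses all 80 patients as a single paired sample. Splitting the sample by mode lowers the power of the paired test. Moving to an independent-samples comparison lowers it much further, because the 80 are then divided into groups that are contrasted with each other. The primary outcome is a set of monthly service measures, to which a Cohen's d on 80 patients does not apply.

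The between-model comparison matters most. The Discussion presents the model as saving money without loss of clinical outcome, and the comparison of motor recovery between staffing models bears on that claim. If 0.99 is taken to cover it, a non-significant result looks far more reassuring than it is.

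**Working it through.** **Inputs.** Two-sided alpha 0.05, d = 0.5 and total N = 80 come from section 2.5. The tests come from section 2.6. The splits below are assumptions, because the article gives none. Two modes are assumed because the named tests are two-sample tests.

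**Formulas (noncentral t).** Power is the probability that |T| exceeds the two-sided 5% critical value, where T is noncentral t with

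- paired or one-sample test: df = n − 1, ncp = d·√n;
- independent samples: df = n1 + n2 − 2, ncp = d·√(n1·n2/(n1 + n2)).

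**Step 1: reproduce the stated figure.**

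- Paired, n = 80: ncp = 0.5 × √80 = 4.472, df = 79, critical t = 1.990, power **0.993**. The Wilcoxon version (asymptotic relative efficiency 3/π) gives 0.991.
- Independent, 40/40: ncp = 0.5 × √20 = 2.236, df = 78, critical t = 1.991, power 0.598 (one-sided 0.716). This does not match.
- Independent, 80 per group: power 0.882. This does not match.

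So 0.99 fits a single paired test on the whole sample. Because section 2.5 names no test, this is inferred from the match.

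**Step 2: the planned tests at the same nominal d.**

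| Split of 80 | Paired, larger mode | Paired, smaller mode | Between models |
|---|---|---|---|
| 40/40 | 0.869 | 0.869 | 0.598 |
| 50/30 | 0.934 | 0.754 | 0.571 |
| 60/20 | 0.968 | 0.565 | 0.481 |
| 70/10 | 0.985 | 0.293 | 0.309 |

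For a fixed total, n1·n2/(n1 + n2) is largest when the groups are equal. The 0.598 is therefore a ceiling for the between-model test and needs no assumption about allocation. The non-parametric alternatives at 40/40 are slightly lower: about 0.85 (Wilcoxon) and 0.58 (Mann–Whitney).

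The 0.869 is a ceiling only for the smaller of two modes, which cannot hold more than 40 patients.

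**Step 3: what the between-model test could detect.** At 40/40, 80% power needs d = 0.634, and any other split needs a larger d. At d = 0.5, 80% power needs 64 per group (128 in all) and 99% power needs 148 per group (296 in all).

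**Step 4: the primary outcome.** The calculation uses a standardised mean difference over 80 patients. The primary measures are monthly counts, minutes, a ratio and falls for the room over one year. No input to the calculation refers to any of them.

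**The case against.** Several points can be made for the authors, and most limit the concern without removing it.

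- **The arithmetic is right, and a pooled comparison is natural.** In a single-group pre-post study a reader would expect a T0–T1 test on everyone, and section 2.3 says the two assessments serve to determine therapy effects. This stands: the fault is a mismatch between the power statement and the analysis plan, which one sentence in section 2.6 could partly mend. As written, though, that sentence is missing.
- **0.99 does not need every patient to finish.** Power is 0.990 at 76 pairs and still rounds to 0.99 at 71 (0.986). This stands.
- **The two values of d differ in kind.** In the paired test d is in SDs of within-patient change. In the between-model test it is in SDs between patients, and section 2.6 does not say whether of change or of the T1 score. So 0.99 and 0.60 are not strictly like for like. But section 2.5 offers one d for the whole study, and applying it to each planned test is a fair check of that claim.
- **The sample size came from admissions, this is a pilot, and the Discussion concedes it is small.** True, so no design decision depends on the figure. The concession sits awkwardly beside a claim of 0.99 power and does not correct it.

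Three stronger readings are tempting and are not supported. A reader might infer that every within-mode test has 0.87 or less; that holds only with equal filling, and a mode of 60 has 0.968. A reader might take the one-year productivity window to mean only 12 × 4 = 48 patients are available; section 2.5 plans 20 months of accrual, and nothing ties the clinical tests to that window. A reader might also infer that the authors intend to read a null between-model result as proof of no difference; the article does not say so, and its expectation of maintained outcomes rests on personalised treatment. That misreading is a risk, not a plan.

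**Conclusion.** Wrong as written. The 0.99 is correct for one pooled paired T0–T1 test on about 80 pairs with d = 0.5 in SDs of change, and section 2.6 contains no such test. At the same nominal d, the planned between-model comparison has at most 0.60 power under any split, so it would miss a moderate difference at least four times in ten (1 − 0.598 = 0.402). That is a shortfall of at least 0.39 from the stated figure (0.99 − 0.60). Within-mode power depends on a split that is not given: at most about 0.87 in the smaller of two modes, and more in a larger one. The figure says nothing about the primary productivity outcome.

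The 0.60 ceiling rests only on d = 0.5, two-sided 0.05 and a total of 80. The 0.87 ceiling also assumes at least two modes. That the 0.99 came from a paired test is an inference from reproduction.

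**What to change.** Restate section 2.5 along these lines:

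- The 0.99 applies only to one pooled paired T0–T1 comparison on about 80 pairs, with d = 0.5 in SDs of change. If that test is intended, add it to section 2.6 for one named motor scale.
- The between-model comparison has at most 0.60 power at d = 0.5 in between-patient SDs. The smallest difference detectable with 80% power is at least about 0.63 SD.
- Within-mode power depends on how patients divide among modes, and is at most about 0.87 in the smaller of two modes. Do not write 40/40 into the text as if it were planned, because the article fixes no split.
- No power is claimed for the productivity outcomes.

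Remove the closing sentence of section 2.5 about the likelihood of detecting effects and the dependability of the findings, or limit it to the pooled test.

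The cost is wording and a less favourable figure. The target of 80 stands, because it was set from admissions and not from power.
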